To calculate the sample size we relied on the hypothesis 1. We conducted a logistic regression analysis having four exposure levels W1/W2, F1, C1 and C2. The highest exposure level is assigned to W1 and W2 (due to their daily exposure to raw and untreated WW and FS), the second highest to F (due to accidentally intake of contaminated water and soil), the third highest to C1 (e.g. due to frequent flooding events) and the lowest to C2 (Blumenthal and Peasey 2002; WHO 2006a). The number of persons in category W1 and W2 is assumed to be limited to 150, the number of F1 to 250, the number of persons in class C1 to 200 while the number of persons in class C2 could be as high as necessary (Table 1).

**Table 3** Selection criteria and potential numbers of exposure groups

| **No.** | **Definition of exposure group** | **Estimated number of individuals** |
| --- | --- | --- |
| 1. **W1** | Worker who operate and work at Bugolobi Sewerage Treatment and Disposal works | 30-50 |
| 1. **W2** | Worker who collect and transport the faecal sludge | 100-150 |
| 1. **F** | Farmers who working within the Nakivubo swap and are exposed to WW and/or FS | 250-500 |
| 1. **C1** | Community in proximity of the wetland but are no farmers | 10,000-20,000 |
| 1. **C2** | Community who live and work approximately 2 km away from the Nakivubo swamp and live ether east of the Port Bell road and west of Kibuli road and Tank Hill road. | 10,000-20,000 |

We aim at a power of 95%, in order to make sure that a reduction in effective exposure variance by 35% still leaves 80% power. Effective exposure variance is the variance of the 4-level exposure variable after regression on potential confounding variables (e.g. socio-economic status). With a variance reduction by 35%, the remaining exposure variance is 65% of the original value, so that the standard deviation after reduction is about 80% of the original exposure standard deviation. This increases the standard error by a factor of 1.25. If we have 80% power with the adjusted standard error (SE) 1.25*SE we may detect an effect of ln(odds ratio (OR)) = (1.96+0.84)*1.25*SE = 3.5*SE = (1.96 + 1.54)*SE. And 1.54 corresponds to slightly less than 95% power with the original unadjusted SE. Clearly, the factor limiting power most strongly is the relatively small size of the highest exposure group (W1, W2).

**Table 4** Results of the logistic regression analysis considering four exposure variable (C1, C2, F1 and W1)

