| Exposure Scenarios | Assumed prevalence rate for C2 | Assumed difference in Odds Ratio between W1/W2 and C2 | Assumed prevalence rates in  C1 / F / W1,W2 | Calculated sample size for each group  C1 / C2 / F1 / W1,2 |
| --- | --- | --- | --- | --- |
| **1** | 40% | 2 | 46 / 51 / 57 | 300 / 200 / 250 / 150 |
| **2** | 30% | 2 | 35 / 40 / 46 | 400 / 200 / 250 / 150 |
| **3** | 20% | 2.5 | 25 / 32 / 38 | 300 / 200 / 250 / 150 |

To anticipate for non-response or missing data, a margin of 25 participants for F, C1 and of 50 for C2 is added resulting in a final sample size of 1000 participants

In view of these considerations and calculations we will plan to conduct our study with the sample size calculated for the exposure scenario 3 (Table 2) and target the following number of people in each group: C1: 350, C2: 225, F1: 275 and W1 and W2 an excessive sample of 50 and 100, respectively and assume a prevalence rate of intestinal parasitic infections of 20% ( Kabatereine et al. 1997; Blumenthal and Peasey 2002;; WHO 2006b) in the lowest exposure group (C2) and an OR between the highest (W1, W2) and lowest exposure group (C2) of 2.5.

- - - 1. Sampling procedures

First, we will sensitise the worker (W1 and W2) study groups while meeting with representatives of each group (WW treatment plant operator, chairman of FS workers) and explain the aims and procedures of the study. Each of the representatives will be asked to prepare a list that contains the names, sex and age of their group members. We aim to select an excessive sample of the two groups approximately 50 for W1 and 100 for W2.

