To select the community groups C1 and C2 we will rely on the population data collected in the census 2012 and characterise the low and middle income settlements restricted to an area around the Nakivubo swamp (population estimate and area characterization for C1 is given in Table 5 and Figure 4). We will focus at a total area of approximately 96 km^2^ and subdivide the area in 96 squares (each square 1km^2^) and exclude all areas which belong to ether high income, industrial or business areas. Further we will describe and map the characteristics (income level, numbers of household) of each square and assign it to ether C1, C2. To get the necessary data we will first consult the data from the national bureau of statistic to have a rough understanding of the social-economic pattern, second our team will go and map the households and estimate the number of people living in each square. Later, we will randomly select (with random numbers) 14 squares for C1 and 9 squares for C2. Within each square we will randomly select 25 households and contact the household members personally to ask if they are willing to participate in the study. If they agree we will make an appointment for an interview and will collect the stool sample the next morning (Figure 5).

Table 5 Population sizes of communities (C1) exposed to Nakivubo swamp

| Area | Zones | Social economic status | Population estimate |
| --- | --- | --- | --- |
| Bukasa parish | Keityabya/Yoka | Low | 5,000 |
|  | Soweto/Kanyogoga | Low | 2,500 |
|  | Namuwongo A | Low | 1,500 |
|  | Namowongo B | Low | 3,000 |
| Muyenga |  | High | 1,500 |
| Nakawa | Port Bell | Low | 3,000 |
|  | Kitintale | Middle | 2,000 |
|  | Bugolobi | Middle | 2,000 |
|  |  | Total | 20,500 |

[figure not shown]

**Figure 4** Map showing communities adjacent to Nakivubo swamp

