Further, we will conduct with each participant a questionnaire interview (will take about 30 min) to assess e.g. their demographic, occupation, intensity and causality of exposure to WW and FS, personal protective equipment, hygienic behaviour and signs and systems of specific health outcomes (ANNEX 10.1). Later, each participant will be provided with a small plastic container which is labelled with their unique ID. Participants will be invited to return the container with a fresh morning stool sample the following day directly to the working place for W1 and W2 and for community member and farmer to an appointed health centre. The anticipated study period for W1 will be 2 days, for W2 5 days, for F 10 days, for C1 5 days and for C2 10 days.

Table 6 Sampling framework for the cross-sectional study

| Exposure group | Total participants | Allocated working days | Selected unit | Participants per unit |
| --- | --- | --- | --- | --- |
| **Worker 1** | 50 | 2 | Excessive sample | 50 workers |
| **Worker 2** | 100 | 10 | Excessive sample | 100 workers |
| **Farmers** | 275 | 10 | 275 randomly selected farmers from pre-compiled list |  |
| **Communities 1** | 225 | 5 | 9 squares (1km^2^) | 25 households (one member per household) |
| **Communities 2** | 350 | 10 | 14 squares (1km^2^) | 25 households (one member per household) |

- - - 1. Inclusion and exclusion criteria

Wastewater treatment plant workers, faecal sludge workers, farmer and community members will not be allowed to participate in the study if they do not fulfill any of the following exclusion criteria:

- too sick to attend school or participate in the study (e.g. severe diarrhoea, severe anaemia, high fever, etc.)
- absence of written informed consent
- person is younger than 18 years of age
  - - 1. Sample analysis

The collected stool samples will be transferred to the laboratory of the Vector Control Division of the MOH on the same day for examination of helminth eggs and intestinal protozoa cysts.

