    - - - 1. *Pre-testing*

To pre-test the questionnaire interviews with the tablet computer and the collection and analysis of stool samples in Kampala, Uganda. Each assistant will interview 3 people who work in the office or lab of BSTDW. The next day we will collect stool samples from the interviewed people and analyse it at the lab of the MOH.

- - - - 1. *Field editing of data*

Data will be entered directly into the data entry mask of the ODK from the assistants during the interviews.

- - - - 1. *Missing data*

Participants are free to not answer any questions or provide a stool sample, in such a case the data entry field will be marked as missing. To anticipate for non-response or missing data, a margin of 25 participants for F, C1 and of 50 for C2 is added resulting in a final sample size of 1000 participants.

- - - 1. Data management and statistical analysis
         1. *Data management*

Every evening the data collected with the tablet computers will be synchronized with a secure server from Swiss TPH in Switzerland where only the main investigators have access to. A random sub sample (100-150 samples) of the collected stool samples will be completely anonymized and transferred to Switzerland for pending polymerase chain reaction (PCR) for species detection and/or meta-genomic analysis in order to provide quantitative insights into microbial population based on sequence data.

- - - - 1. *Statistical analysis*

First, data cleaning will be carried out using STATA version 12. In a next step, descriptive statistics will be used to calculate the distribution of the above mentioned dependent and independent variables within each exposure group.

A first analysis is to test hypothesis 1. Hence, a multilevel regression analyses, adjusting for confounding, will be used to measure the associations between dependent variables (disease outcomes) and independent representing the exposure to WW and FS and to calculate Odds ratios to measure the strength of the associations and to compare the exposure groups.

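### The C1 and C2 recruitment targets and square counts in sections 4.2.1.2 and 4.2.1.3 are the reverse of Table 6, so the size of the reference group is undefined

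*Combined protocol and SAP*

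**What the plan says.** Section 4.2.1.2 (Sample size calculations) sets the inputs to the calculation: "the number of persons in class C1 to 200 while the number of persons in class C2 could be as high as necessary". Table 4 then lists sizes under the header order C1, C2, F1, W1/2. Scenario 3, the one adopted, reads 300, 200, 250, 150. The allowance for non-response follows: "a margin of 25 participants for F, C1 and of 50 for C2 is added". The same sentence is repeated under Missing data (4.2.1.7.5). The section ends with the decision to "target the following number of people in each group: C1: 350, C2: 225, F1: 275", with 50 W1 and 100 W2.

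Section 4.2.1.3 (Sampling procedures) turns this into a draw: "we will randomly select (with random numbers) 14 squares for C1 and 9 squares for C2", with 25 households per square. Table 6, in the same section, has the rows "Communities 1 | 225 | 5 | 9 squares (1km^2" and "Communities 2 | 350 | 10 | 14 squares (1km^2". The columns are total participants, working days and selected unit. The text above Table 6 and the timetable also give C1 5 field days and C2 10.

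**The concern.** The text and Table 6 are both field instructions and cannot both be followed. One puts 350 people and 14 squares in the partly exposed community (C1); the other puts them in the unexposed community (C2). C2 is the low end of the odds ratio of 2.5 on which section 4.2.1.2 sizes the study, and it is the one group which that section allows to grow. If the text is followed and Table 6 was meant, the extra people go to the wrong group, and the reference group has 9 clusters instead of 14 in an analysis planned as multilevel. Once squares are drawn and stool is collected, this cannot be undone within the three-month timetable.

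**Working it through.** **1. The two versions side by side**

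| Source | C1 | C2 |
|---|---|---|
| 4.2.1.2, final targets | 350 | 225 |
| 4.2.1.3 text, squares × 25 | 14 × 25 = 350 | 9 × 25 = 225 |
| Table 6 | 225 (9 squares) | 350 (14 squares) |

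Totals: 350 + 225 + 275 + 150 = 1000 and 225 + 350 + 275 + 150 = 1000. The abstract gives only 575 community members, which fits both.

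**2. Which version follows from the plan's own inputs**

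- C1 limit plus margin: 200 + 25 = 225. Scenario 3's free group plus the C2 margin: 300 + 50 = 350. This is Table 6.
- Table 4 read by its printed header, plus margins: C1 300 + 25 = 325, C2 200 + 50 = 250. This matches neither version, and it also totals 1000.
- To reach 350/225 from the printed header, the margins must be exchanged: 300 + 50 and 200 + 25.
- In Table 4 the entry labelled C2 is 200 in all three scenarios, and the entry labelled C1 is 300, 400, 300. That is the stated rule (C1 fixed at 200, C2 free) with the labels exchanged.
- Field load under Table 6: 225/5 = 45 and 350/10 = 35 people per day. Under the text: 350/5 = 70 and 225/10 = 22.5.

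**3. The plan's power statement**

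The plan writes "1.96+0.84)*1.25*SE = 3.5*SE = (1.96 + 1.54)*SE". Check: 2.80 × 1.25 = 3.50 and 3.50 − 1.96 = 1.54, and Φ(1.54) = 93.8%, which the plan itself calls slightly less than 95%. Its goals are 95% power unadjusted and 80% after losing 35% of the exposure variance.

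**4. Power under scenario 3** (C2 prevalence 20%, OR 2.5, two-sided 5%)

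*Trend test, 1 df, at the final targets.* Scores C2 = 0, C1 = 1/3, F = 2/3, W = 1. The fitted prevalences are 20, 25.3, 31.5 and 38.5%, close to Table 4's 20, 25, 32 and 38%. SE = 1/√Σw(x − x̄)², with w = np(1 − p). Power = Φ(ln 2.5/SE − 1.96), with ln 2.5 = 0.916. For the 35% loss, SE is divided by √0.65.

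| Allocation | SE | Unadjusted | After 35% loss |
|---|---|---|---|
| C1 350, C2 225 | 0.216 | 98.9% | 92.7% |
| C1 225, C2 350 | 0.198 | 99.6% | 96.1% |

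*W1/W2 against C2 only, before margins.* W prevalence = 0.625/1.625 = 38.5%. SE² = 1/(150 × 0.385 × 0.615) + 1/(n × 0.2 × 0.8).

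| C2 analysed | SE | Unadjusted | After 35% loss |
|---|---|---|---|
| 200 | 0.244 | 96.4% | 85.8% |
| 300 | 0.221 | 98.5% | 91.6% |

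**5. Clustering by square** (the documents give no ICC, so these values are assumptions)

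The C2 variance term is multiplied by 1 + (m − 1) × ICC, with m = 200/9 or 300/14, in addition to the 35% loss. W1/W2 against C2:

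| ICC | C2 200 in 9 squares | C2 300 in 14 squares |
|---|---|---|
| 0.01 | 82.0% | 89.3% |
| 0.05 | 68.0% | 79.6% |
| 0.10 | 54.9% | 68.5% |

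**The case against.** Three replies deserve weight.

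First, the larger C1 is not a lone slip. Table 4's header, the targets and the square counts all agree on it, and the limit of 200 on C1 is unexplained: Table 3 estimates 10,000–20,000 people for C1 as for C2, and Table 5 totals 20,500. This stands to the extent that the intended order is an inference. The inference is strong, because the limit, the margins and the field days agree with each other and with Table 6, while the printed targets do not follow from the printed table and margins.

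Second, a reader might infer that power calculations prove Table 4's labels wrong. They do not. On the 1-df trend the printed order gives 93.1% and 92.2% for scenarios 1 and 2, and the exchanged order 96.3% and 97.3%. But the plan tolerates slightly less than 95%, and a 3-df test fits printed scenario 3 well (94.8%; 80.7% after the variance loss). No single test reproduces all three rows.

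Third, a reader might infer that following the text leaves Hypothesis 1 underpowered. The plan's own inputs do not support that. Both allocations exceed 95% unadjusted and 80% adjusted, and the loss is about 1 to 6 points. The larger losses rest on an assumed ICC and on the pairwise contrast. On the trend at the final targets, with a design effect of 1 + 24 × ICC applied to C1 and C2, adjusted power at ICC 0.05 is 78.9% against 85.0%.

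**Conclusion.** The contradiction holds and affects field conduct. It lies within each section: the margins against the targets in 4.2.1.2, and the text against Table 6 in 4.2.1.3. At issue are 125 people (350 − 225) and 5 squares (14 − 9) in the reference group. Table 6 is very probably the intended allocation, but only the authors can confirm it. The need to correct rests on two incompatible recruitment instructions, not on a failed power target. Under scenario 3 without clustering the cost in power is modest. Under an assumed ICC of 0.01 to 0.10, stacked on the 35% loss, the pairwise gap is about 7 to 14 points (89.3 − 82.0 = 7.3; 68.5 − 54.9 = 13.6).

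**What to change.** Before any square is drawn, the authors should confirm the intended C1/C2 allocation and make every place agree. If Table 6 is confirmed:

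- Section 4.2.1.2, targets: C1 225, C2 350.
- Section 4.2.1.3, text: 9 squares for C1 and 14 for C2.
- Table 4, last column header: C2 / C1 / F / W1,2.

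The margin sentences and Table 6's community rows then stand as they are. Limit the change to C1/C2 counts, squares and labels. Table 6 should not be adopted wholesale, because it gives W2 10 working days where the text above it gives 5; that separate conflict needs its own reconciliation. The cost is protocol wording only: the total stays at 1000, and no participants or field days are added.

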To select farmers (F1) we have to first describe and map the on-going farming activities within the Nakivubo swamp and channel. To estimate the number of farmers our research team will compile a list with the contact details (name, phone number and GPS coordinates where the framing activity takes place) of farmers who would be interested to participate in this study on two successive days, once in morning between 9-11 am and once in the afternoon 2-4 pm. Later we will randomly select 275 framers from this list and contact them to arrange an individual meeting to inform them about the study objective. If they agree to participate, we will make an appointment for interviewing and collect the stool sample the next morning (Figure 5).

[figure not shown]

**Figure 5** Grid-system for the selection of community and farmer groups in the area around the Nakivubo swamp. Red squares indicate **(C1)** communities which are potentially exposed by WW and FS e.g. live in areas close to the Nakivubo swamp, transparent squares indicate **(C2)** communities which live approximately 2 km away from the Nakivubo swamp, hence, we assume that these groups are not directly exposed to the WW and the FS and green squares indicate **(F)** areas within Nakivubo swamp where farming takes place.

Each of the selected study participants will be informed on the study objectives, procedures, and potential risks and benefits. People will be invited to participate in the study. As re-emphasized under the chapter ‘Ethical considerations’, persons who are interested to participate in the study will have to sign an informed consent (ANNEX 10.2). We will only select persons aged 18 years and above.

Once the written informed consent has been obtained, each participant will get a unique ID (4 digits e.g. 0001; (i) 1-5, which indicates the exposure group (1 = W1; 2 = W2; 3 = F1, 4 = C1, and 5 = C2); (ii-iv) 1-350 which indicates the individual in the group).

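### C1 and C2 prevalences over-represent sparse squares and small households, because squares are drawn without regard to size, 25 households are taken from each, and no weights or within-household selection rule are planned

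*Combined protocol and SAP*

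**What the plan says.** Section 4.2.1.3 (Sampling procedures) sets out the community sample in stages.

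- **Mapping.** Before any draw, "second our team will go and map the households and estimate the number of people living in each square". The stated use is to describe each square and assign it to C1 or C2. High income, industrial and business areas are excluded.
- **Squares.** "Later, we will randomly select (with random numbers) 14 squares for C1 and 9 squares for C2". No size measure is mentioned, so equal probability within each group is the plain reading, although it is not stated literally.
- **Households.** "Within each square we will randomly select 25 households and contact the household members personally to ask if they are willing to participate". The take is 25 whatever the number of households in the square. Those who agree get an appointment.
- **Persons.** Table 6 gives "25 households (one member per household" and the same section adds "We will only select persons aged 18 years and above". No rule for choosing the member, calling back or replacing a household is given.

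For analysis, section 4.2.1.8.2 says "descriptive statistics will be used to calculate the distribution of the above mentioned dependent and independent variables within each exposure group". It then tests hypothesis 1 with "a multilevel regression analyses, adjusting for confounding, will be used to measure the associations between dependent variables (disease outcomes") and the exposure variables. Sampling weights appear nowhere.

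**The concern.** An equal-probability draw of areas followed by a fixed take per area is not self-weighting. Each selected square contributes the same number of people, however many live there, and each household contributes one person, however many adults it holds. An unweighted group prevalence then describes an average over squares and households rather than over residents.

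This matters because prevalence of infection is a named dependent variable (4.2.1.6.1), objective 1 is to assess and map risk (section 3), and the QMRA results are to be validated against the objective 1 infection data (4.2.3.1). C2 is also the reference group for hypothesis 1, so an error in its prevalence enters every crude comparison with it.

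The community groups are the only ones left open at person level. Farmers are drawn at random from a compiled list, and workers are listed by name, sex and age.

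**Working it through.** **1. The plan's own counts.** 14 × 25 = 350 and 9 × 25 = 225. With 275 farmers and 150 workers, 350 + 225 + 275 + 150 = 1000, as stated. Section 4.2.1.3 and the sample size text give C1 14 squares (350) and C2 9 (225). Table 6 gives C1 9 squares (225) and C2 14 (350).

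**2. Inclusion probability.** Let m be the squares drawn, M the eligible squares in the group (not stated), H the households in the square and A the adults in the household. If the member is chosen at random,

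P(person) = (m/M) × (25/H) × (1/A).

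m, M and 25 are constant within a group, so P is proportional to 1/(H × A). An adult in a four-adult household has 0.25 times the chance of an adult living alone in the same square. If the member is not chosen at random, the last factor is unknown.

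**3. How unequal sizes might be.** Table 5 is the only size information, and it covers C1 zones, not squares. Assume that its seven low and middle income zones stand in for squares: 5,000, 2,500, 1,500, 3,000, 3,000, 2,000 and 2,000, total 19,000.

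- Equal take gives each zone 1/7 = 14.3% of the sample.
- The largest holds 5,000/19,000 = 26.3% of the people, so it is represented at 0.143/0.263 = 0.54 of its share.
- The smallest holds 1,500/19,000 = 7.9%, so it is represented at 0.143/0.079 = 1.81 of its share.

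**4. Effect on prevalence (assumed link).** Let prevalence rise linearly with zone size from 15% to 35%.

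- Unweighted: mean size 19,000/7 = 2,714; 0.15 + 0.20 × (2,714 − 1,500)/3,500 = 21.9%.
- Population-weighted: the sum of squared sizes is 59.5 million and 59.5 million/19,000 = 3,132; 0.15 + 0.20 × (3,132 − 1,500)/3,500 = 24.3%.
- With the same prevalence in every zone, the two figures are equal.

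**5. A wider range (assumed).** Suppose half the squares are dense, with r times the households of the rest, and prevalence is d higher in dense squares. Bias = −(0.5 − 1/(1 + r)) × d.

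- r = 2, d = 5 points: −(0.5 − 0.333) × 5 = −0.8 points.
- r = 10, d = 20 points: −(0.5 − 0.091) × 20 = −8.2 points.
- If infection is commoner in sparse squares, the sign reverses.

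**6. Cost of weighting.** For the zones in step 3, the Kish factor is 7 × 59.5/361 = 1.15 (with 361 million = 19,000²). The effective sample is 350/1.154 = 303 or 225/1.154 = 195. This covers the square stage only; weights for the number of adults would add to it.

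**The case against.** The strongest reply is that hypothesis 1 is tested by an adjusted model. Sections 4.2.1.6.2 and 4.2.1.7.2 collect age, gender, salary, household size, property, hygiene, and water and food consumption. Much of what would link density to infection is therefore measured, and the frame is already narrowed to low and middle income settlements. Equal-probability squares also spread the sample over the area, which suits mapping and the distance hypothesis. All of this stands, and it limits the point mainly to the descriptive prevalences. The multilevel model can handle clustering by square, but neither it nor covariate adjustment restores population shares in those prevalences.

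Two stronger readings are tempting.

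- **That the C2 prevalence is too low and the odds ratio of 2.5 inflated.** Suppose half the squares have three times the households of the rest, with 28% infected against 12%. True prevalence is (3 × 0.28 + 0.12)/4 = 24%, the equal-take figure is 20%, and the crude odds ratio against workers at odds 0.625 is 0.625/(0.24/0.76) = 1.98 rather than 2.50. But these prevalences are assumed, and the calculation is crude. They also imply an odds ratio of (0.28/0.72)/(0.12/0.88) = 2.85 between squares within one unexposed group, more than the worker effect the study is designed to detect. Table 5 says nothing about C2. In a milder case (r = 2, d = 10 points) the bias is 1.7 points, against a simple standard error of √(0.2 × 0.8/225) = 2.7 points.
- **That whoever is at home and willing will be interviewed.** The documents only omit the selection rule. Households are drawn at random, members are contacted personally and an appointment is made. Willingness is a consent requirement in every group.

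**Conclusion.** The point holds for the C1 and C2 prevalences. On the plain reading of the draw, people in sparse squares and small households are over-represented, and nothing in the analysis corrects for it. That follows from the stated design.

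Whether it biases prevalence, by how much and in which direction depends on a link between infection and density or household size that the documents do not describe. With no link the bias is zero. Under the assumed inputs it runs from −0.8 to −8.2 points, and it could equally be positive.

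The documents do not support a statement that the hypothesis 1 odds ratio is wrong. Adjusted odds ratios are likely to be less affected, though how much less cannot be shown from the text.

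**What to change.** 1. Use the household counts already planned, in one of two ways. Either draw squares with probability proportional to household count and keep the take of 25, which gives every household in a group the same chance, m × (H/ΣH) × 25/H = 25m/ΣH (provided no square's m × H/ΣH exceeds 1). Or keep the present draw and report C1 and C2 prevalences weighted by inverse inclusion probability. The second keeps the geographic spread.
2. In each selected household, list the adults aged 18 and over, select one at random, and record the number of eligible adults for the weight. State a call-back rule and record non-response.
3. Keep the adjusted multilevel model as the main analysis of hypothesis 1.
4. Reconcile the C1 and C2 square counts (14 and 9 in the text, 9 and 14 in Table 6) before the draw.

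No extra participants are needed. Weighting for squares loses precision, by a factor of about 1.15 on the Table 5 assumption, and weighting for adults adds some more. Listing adults and revisiting costs field time in a tight schedule: Table 6 implies 225/5 = 45 C1 and 350/10 = 35 C2 interviews a day, with four assistants. This should be settled before fieldwork, because household composition that is not recorded cannot readily be recovered later.

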For each stool sample duplicate Kato-Katz thick smears will be prepared, using standard 41.7 mg template. The slides will be labelled with the participants unique ID plus ether ‘A’ (first Kato-Katz) or ‘B’ (second Kato-Katz) and allowed to dry for at least 30 minutes. Slides will be examined quantitatively under a light microscope by 1 laboratory technicians. For each slide the number of helminths (*A.lumbricoides*, hookworm, *T.trichiura* and *S.mansoni* and other helminth) will be counted and recorded separately.

Additionally, for each stool sample we will perform a FECT to detect protozoa infections. In short, approximately 1 g of the stool will be placed in a tube containing 10 ml of formalin and labelled again with the unique ID number of the participant plus a C. The sample will be mixed, centrifuged and the supernatant removed. 7 ml saline solution will be added, mixed and centrifuged. The sediment is the examined on presence of helminth eggs and intestinal protozoa cysts under a light microscope.

For quality control 10% of all the Kato-Katz slides will be re-examined by an external person (e.g. PhD student), the results of the *A.lumbricoides, T.trichiura* and *S.mansoni* egg counts compared and any discrepancies removed by re-examining the discordant slides.

A subset of the stool samples (100-150 samples) will be frozen (-20°C) and transferred to Swiss TPH in Switzerland for pending polymerase chain reaction (PCR) for species detection and/or meta-genomic analysis in order to provide quantitative insights into microbial population based on sequence data.

- - - 1. Study variables for the cross sectional survey
         1. *Dependent variables*

As dependent variables we will measure the prevalence of all detected parasitic infection (helminth and intestinal protozoa) and the intensity of helminth infections in the stool samples. For the questionnaire study we will ask the participants questions about symptoms and signs of certain disease outcomes to estimate the prevalence of fever and skin, eye, reparatory diseases and diarrhoea episodes within a two week recall period.

- - - - 1. *Independent variables*

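### The exposure-group code is the first digit of the ID on every stool container, slide and tube, and no masking of the microscopy is described

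*Combined protocol and SAP*

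**What the plan says.** Section 4.2.1.3 (Sampling procedures) defines the identifier as a four-digit number whose first digit is "1-5, which indicates the exposure group", with the key "1 = W1; 2 = W2; 3 = F1, 4 = C1, and 5 = C2". The other three digits number the individual within the group. For stool collection, "each participant will be provided with a small plastic container which is labelled with their unique ID".

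Section 4.2.1.5 (Sample analysis) carries the identifier into the laboratory. For Kato-Katz, "The slides will be labelled with the participants unique ID plus ether" A or B. The FECT tube is "labelled again with the unique ID number of the participant plus a C". On reading, the plan says: "Slides will be examined quantitatively under a light microscope by 1 laboratory technicians". An external person, with the PhD student as the example, re-examines 10% of the Kato-Katz slides. Counts of *A. lumbricoides*, *T. trichiura* and *S. mansoni* are compared, and discordant slides are looked at again.

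Parasite prevalence and helminth intensity, both read at the microscope, are dependent variables in Section 4.2.1.6.1. They feed hypothesis 1 (an odds ratio of 2.5 or higher) and hypothesis 2 (helminth intensity falling with distance).

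**The concern.** Kato-Katz and FECT results depend on how long and how carefully a reader searches, above all in light infections. A reader who can tell a sludge worker's slide from a distant resident's may search the two differently without intending to. The expected direction is stated in advance in Section 3, so such a difference would more naturally favour the hypotheses than oppose them.

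This would be outcome misclassification that differs by exposure group. The confounder adjustment planned in Section 4.2.1.8.2 cannot remove it, and once slides have been read with the group visible, the analysis cannot recover unbiased counts. Both hypotheses are exposed: hypothesis 1 directly, and hypothesis 2 because group and distance are linked by design (C2 is chosen at about 2 km from the swamp). The stakes are raised by Section 1.3, where the investigators aim to establish a causal relation between exposure level and disease.

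**Working it through.** **Step 1. Trace the label.**
- ID defined, first digit = group: Section 4.2.1.3.
- Container carries the ID: Section 4.2.1.3.
- Slides carry the ID plus A or B, and the FECT tube the ID plus C: Section 4.2.1.5.
- No re-coding step stands between any of these.

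**Step 2. Look for a safeguard elsewhere.**
- Section 5.2 codes test results so that they cannot be tied to names. That protects confidentiality, but a code that starts with the group digit still shows the group.
- Section 4.2.1.8.1 anonymises stool samples, but only the 100-150 sent to Switzerland for PCR or metagenomics, not the microscopy.
- No masking, re-labelling or random reading order is described for the primary, quality-control or discordant reads.

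**Step 3. What the quality control covers.** The budget allows 1,000 × 2 = 2,000 Kato-Katz slides, so the re-read is 0.10 × 2,000 = 200 slides. FECT results get no second read. Hookworm is counted on the slides but is not among the species listed for comparison.

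**Step 4. Size, by illustration.** The plan states no figure for this, so there is none to reproduce.

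Input from the plan: C2 prevalence p = 20% (Section 4.2.1.2, scenario 3). Assumed, because the documents give no reader accuracy: sensitivity Se by group, and specificity 100%. With perfect specificity:

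apparent prevalence = p × Se; apparent OR = [a/(1 − a)] / [b/(1 − b)], where a is the exposed group and b the control group.

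True OR = 1, so p = 0.20 in both groups, with control sensitivity 60%: b = 0.20 × 0.60 = 0.12.
- Exposed 70%: a = 0.14; OR = (0.14/0.86)/(0.12/0.88) = 0.1628/0.1364 = 1.19.
- Exposed 75%: a = 0.15; OR = (0.15/0.85)/(0.12/0.88) = 0.1765/0.1364 = 1.29.
- Exposed 80%: a = 0.16; OR = (0.16/0.84)/(0.12/0.88) = 0.1905/0.1364 = 1.40.

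True OR = 2.5: the exposed odds are 0.25 × 2.5 = 0.625, so p = 0.625/1.625 = 38.5%, which agrees with the 38% in Table 4 to within rounding.
- Equal sensitivity of 70%: a = 0.2692, b = 0.14; OR = (0.2692/0.7308)/(0.14/0.86) = 2.26.
- 80% v 60%: a = 0.3077, b = 0.12; OR = (0.3077/0.6923)/(0.12/0.88) = 3.26.

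Equal imperfect sensitivity pulls the OR below 2.5. A 20-point gap favouring the exposed group carries it above 2.5.

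**The case against.** The strongest reply is that the plan is silent on masking; it does not say that reading is open. Three stronger readings are tempting, and the documents do not support them.

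- **That the readers know the group.** The text does not say that laboratory staff receive the digit key. They are existing staff of the health ministry's laboratory, and the PhD student is only an example of a second reader. The sample ID, 0001, does not even begin with a code from 1 to 5. What stands is that the explicit rule makes the group readable, and a first digit with five values is easy to decode. Nor is it certain that one person reads everything: the single technician is mentioned for Kato-Katz and could mean one reader per slide, and the number of FECT readers is not given.
- **That each laboratory day holds one group, so that reader drift is tied to exposure.** Section 4.2.1.3 gives only durations: "The anticipated study period for W1 will be 2 days, for W2 5 days, for F 10 days". (Table 6 gives W2 10 days, which should be reconciled.) The timetable cells are blank in the available text, and F, C1 and C2 share one organising row, so collection may overlap. Batching by group is possible but not established.
- **That the re-read cannot detect the problem.** An external reader without the first reader's tendency could expose under-counting, and discordant slides are re-examined. The check is weak for the reasons in Step 3 of the working, but it is not useless.

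It is also fair to say that the sensitivity gaps are hypothetical, and that from a true OR of 1 the apparent ORs of 1.19 to 1.40 stay well below 2.5. They would still raise the chance of a false finding against an OR of 1.

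**Conclusion.** The concern holds in this form: following the stated labelling rule puts the exposure group in front of everyone who reads the stool microscopy, and the plan describes nothing to mask it. That goes beyond a missing detail, because the rule itself creates the exposure. The bias, if it occurs, would most plausibly run in the hypothesised direction.

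Its size cannot be known from the documents. With assumed sensitivity gaps of 10 to 15 points at the plan's 20% prevalence, a true OR of 1 would appear as 1.19 to 1.29. These figures assume perfect specificity and show scale only. The label trace is certain. Whether readers would decode or act on the label is not, and the conclusion does not depend on proving that they would. The change should be made before labels are printed.

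**What to change.** 1. Use an ID or laboratory number with no group code, assigned or re-labelled at laboratory reception by someone who does not read slides. Hold the key outside the laboratory. Re-labelling at reception matters because workers return samples at the workplace and farmers and residents at a health centre (Section 4.2.1.3), so a neutral ID alone would leave the delivery route revealing worker status.
2. State in Section 4.2.1.5 that the primary, quality-control and discordant re-reads, for both Kato-Katz and FECT, are masked to exposure group.
3. Where collection days allow, mix slides from different groups in the reading order.

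The cost is a small re-labelling and key-keeping task. Mixing across groups is limited by same-day processing and field logistics, so item 3 should stay conditional.
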